## 8.2 Sample Size Justification

The primary end point is the rate  $\pi$  of SVR. The main objective of the study is to compare the SVR rates of a treatment extension of 24 or 12 weeks in comparison with  $\pi_0=70\%$ , the rate which can be assumed for SVR rates without treatment prolongation from historical data of 24 weeks overall treatment duration.

According to the study design and the main objective, a one-sided test for proportions with a significance level of  $\alpha=5\%$  will be used. The primary statistical analysis will use an ITT approach (all randomized patients who received at least one PEG-Interferon injection). Sample size is chosen such that not only the primary statistical analysis but also the main secondary statistical analysis has a high power and that a comparison of both treatment groups which will be done as further secondary statistical analysis still has a power above 50%.

Power calculation is based on assuming an improved rate of SVR of  $\pi_{24 \text{ ext}}=95\%$  for Group A and of  $\pi_{12 \text{ ext}}=85\%$  for Group B which will be compared with the rate of SVR of  $\pi_0=70\%$ , respectively. Then we obtain a power of at least 90 %, if ITT information of at least 75 patients in Group B is available (main secondary statistical analysis) and a power of nearly 100% if ITT information of at least 75 patients in Group A (primary statistical analysis), is available. The power to prove a statistical difference between Group A and B (further secondary analysis) with a one-sided test and  $\alpha=5\%$  is 55% (using continuity correction).

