### **3.3 Assignment to Treatment Groups**

150 patients with chronic hepatitis C virus infection of the genotypes 2 and 3 shall be enrolled. Patients will be randomized 1:1 in group A (75 patients) and B (75 patients). Stratification factors will be sex, age, genotype, cirrhosis, and the HCV RNA level > 600.000 IU/ml before the ongoing therapy.

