## 8 STATISTICAL METHODS AND SAMPLE SIZE

### 8.1 *Statistical Methods*

The primary statistical analysis will be the comparison of rates for SVR in the ITT population (all randomized patients who received at least one PEG-Interferon injection) in the group with a prolongation of treatment by 24 weeks and a total treatment duration of 48 weeks (Group A) in comparison with the SVR rates in patients without treatment prolongation. The SVR rates of the latter group are assumed to be  $\pi_0=70\%$  from historical data. According to the study design and the main objective, a one-sided test for proportions with a significance level of  $\alpha=5\%$  will be used to test the following hypothesis:

$$H_0: \pi_0 = \pi_{24 \text{ ext}} \text{ versus } H_1: \pi_0 \leq \pi_{24 \text{ ext}}$$

As main secondary statistical analysis, an analogous test is performed for Group B (treatment prolongation by 12 weeks for a total treatment duration of 36 weeks), again with a significance level of  $\alpha=5\%$ .

$$H_0: \pi_0 = \pi_{12 \text{ ext}} \text{ versus } H_1: \pi_0 \leq \pi_{12 \text{ ext}}$$

As further secondary statistical analysis, a comparison of SVR rates of Group A and Group B is planned, testing the one-sided hypothesis

$$H_0: \pi_{12 \text{ ext}} = \pi_{24 \text{ ext}} \text{ versus } H_1: \pi_{12 \text{ ext}} \leq \pi_{24 \text{ ext}}.$$

Further explorative analysis are planned to compare clinical variables and secondary end points between Group A (48 weeks) and B (36 weeks) with appropriate statistical methods as, e.g., Fishers exact test,  $\chi^2$  test, t-test, Mann-Whitney U test and corresponding confidence intervals will be used. Typically, tests will use a significance level of  $\alpha=5\%$  and can be one- or two-sided. Further explorative statistical analysis, e.g., the analysis of predictors for SVR may be used if appropriate.

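### The power for the only randomised SVR comparison (A versus B) rests on a conservative continuity-corrected test; naming Boschloo's exact test would usually gain about 4 to 9 points at no cost

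*Protocol*

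**What the plan says.** Protocol section 8.1 makes the primary and main secondary analyses single-arm tests of Group A and Group B against a historical SVR of 70%. It then says: "As further secondary statistical analysis, a comparison of SVR rates of Group A and Group B is planned, testing the one-sided hypothesis". No test statistic is attached to that hypothesis. A later sentence offers "appropriate statistical methods as, e.g., Fishers exact test" and several other procedures, but for explorative comparisons of clinical variables and secondary endpoints.

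Section 8.2 assumes SVR of 95% in Group A and 85% in Group B, and says that the power to show a difference between them "with a one-sided test and" alpha of 5% "is 55% (using continuity correction". Its stated aim is that this comparison as "further secondary statistical analysis still has a power above 50" per cent. Section 3.3 gives the arm sizes: "Patients will be randomized 1:1 in group A (75 patients) and B (75 patients".

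**The concern.** Section 2 gives the comparison of 12 with 24 weeks of extension as the study objective, and A versus B is the only SVR contrast protected by randomisation. It also has the lowest power of the three planned tests: 55%, against nearly 100% for Group A and at least 90% for Group B versus the historical rate.

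A continuity correction subtracts a fixed amount from the observed difference. With 75 per arm and SVR close to 1, that amount is large relative to the standard error, so a nominal 5% test rejects too rarely when the arms are equal. The unused type I error is unused power. If the analysis uses the test on which the power was based, the trial gives up power it could keep without more patients.

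**Working it through.** **Inputs (protocol sections 3.3 and 8.2).** n = 75 per arm, SVR 95% (A) and 85% (B), one-sided alpha 5%, continuity correction, stated power 55%.

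**Step 1: reproduce the 55%.**
- Mean rate = (0.95 + 0.85)/2 = 0.90.
- SE under equality = √(2 × 0.90 × 0.10 / 75) = 0.04899.
- SE under the alternative = √((0.95 × 0.05 + 0.85 × 0.15) / 75) = 0.04830.
- Continuity correction = ½(1/75 + 1/75) = 0.01333.
- Power = Φ[(0.10 − 0.01333 − 1.645 × 0.04899) / 0.04830] = Φ(0.126) = 55.0%.

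This matches the protocol. Without the correction the same formula gives Φ(0.402) = 65.6%.

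**Step 2: true type I error and power at 75:75.** For each test, sum the product of the two binomial probabilities over every pair of outcomes (0 to 75 in each arm) in which it rejects. The Boschloo test orders outcomes by the one-sided Fisher p-value. Its cut-off is the largest that keeps the maximum rejection rate, over all common SVR values, at or below 5% (here a Fisher p-value of 0.0655).

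| Test | Size at SVR 85% | 90% | 95% | Maximum size | Power, 95% vs 85% |
|---|---|---|---|---|---|
| Corrected z | 3.0% | 2.5% | 1.7% | 3.8% | 54.8% |
| Fisher exact | 3.1% | 3.1% | 2.0% | 3.8% | 58.7% |
| Boschloo | 4.3% | 4.0% | 3.4% | 4.97% | 63.4% |
| Uncorrected z | 5.3% | 5.2% | 5.9% | 6.2% | 68.2% |

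The gain of Boschloo over the corrected test is 63.4 − 54.8 = 8.6 points. Merely dropping the correction is not a valid substitute, because the uncorrected test exceeds 5%. At a common SVR of 70 to 80% the corrected test's size is about 3.3 to 3.4%.

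**Step 3: a single data set.** Take 72/75 versus 66/75. The pooled rate is 138/150 = 0.92 and the SE is √(0.92 × 0.08 × 2/75) = 0.0443. The corrected z is (0.08 − 0.0133)/0.0443 = 1.50, below 1.645, and Fisher p = 0.065, so neither rejects. Boschloo p = 0.048 rejects.

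**Step 4: how stable is the gain?**

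*Other rates, 75:75 (corrected test to Boschloo):*
- 92% vs 82%: 47.5% to 54.1%, gain 6.6.
- 90% vs 80%: 44.1% to 50.3%, gain 6.2.
- 85% vs 75%: 38.1% to 43.8%, gain 5.7.

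*Other arm sizes (A:B), 95% vs 85%:*
- 74:74: 54.0% to 62.8%, gain 8.7 (from unrounded figures).
- 75:73: 56.2% to 61.6%, gain 5.4.
- 72:74: 54.8% to 60.0%, gain 5.2.
- 74:75: 55.5% to 59.7%, gain 4.2.
- 75:74: 57.6% to 59.7%, gain 2.2 (from unrounded figures).
- 70:70: 51.0% to 57.5%, gain 6.6 (from unrounded figures).

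There are 14 ways to lose one to four patients in total from 75:75. Enumerating all of them at 95% vs 85% gives Boschloo power of 59.7 to 62.8%. The gain is 4.2 to 8.9 points in 13 of them, and 2.2 points at 75:74, where the discreteness happens to favour the corrected test.

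**The case against.** The strongest reply is that the document contains no defect. The 55% reproduces exactly and meets the protocol's own aim of more than 50%. The corrected test controls type I error, and a correction in a sample-size formula is a common conservative device that does not bind the analysis. Test choice for a further secondary comparison is often left to the SAP, which is not at hand. Much of this stands, and it rules out several stronger readings that a reader might draw:

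- *That 55% is a miscalculation.* It is not (Step 1).
- *That the protocol commits the analysis to the corrected test.* The correction appears only in the power statement. The loss is real only if the analysis follows that basis.
- *That Fisher's test is planned for A versus B.* Section 8.1 lists it only for explorative comparisons.
- *That about 9 points are always lost.* That figure belongs to a few configurations such as exactly 75:75. The ITT definition requires at least one injection, so small and unequal losses are likely, and the gain is then usually smaller. Against Fisher at 75:75 it is 63.4 − 58.7 = 4.7 points.

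Randomisation is also stratified on five factors (section 3.3), which an unstratified Boschloo test ignores. A stratified analysis in the SAP would be a legitimate alternative; its power was not computed here.

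The objection does not remove the point that 8.2 justifies the comparison with a conservative test while 8.1 names no other. If the SAP uses a different test, the 55% does not describe the planned analysis.

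**Conclusion.** The point holds as an efficiency improvement. The corrected test behind the stated power is valid but runs at about 1.7 to 3.0% rather than 5% when SVR is 85 to 95% with 75 per arm. A valid exact test usually gains about 4 to 9 points, reaching 63.4% at exactly 75:75 and about 60 to 63% after losing one to four patients. These figures rest on the protocol's assumed 95% and 85%, on independent binomial outcomes, and on an unstratified analysis.

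The choice can matter against the protocol's own aim: at 90% versus 80%, the same 10-point difference, the corrected test falls below 50% (44.1%) and Boschloo just reaches it (50.3%). It does not make the comparison well powered; at just over 60% it remains weak for the contrast named as the study objective.

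**What to change.** In section 8.1, name Boschloo's exact unconditional test, one-sided at 5%, for the A-versus-B comparison of SVR, unless the SAP already specifies a stratified test or another valid test without continuity correction. In section 8.2, restate the power for whichever test is named. For Boschloo that is about 60 to 63% at 95% versus 85% with about 75 per arm. Quote it as a range, because it moves with small changes in the ITT numbers. If a stratified test is chosen, its power must be calculated separately.

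The cost is two sentences and a standard software call. No patients are added, and type I error stays at or below 5%.

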## 8.3 Historical control group

| Ref.  | Treatment regimen                                                               | Patients without RVR                           | SVR
without RVR               |
|-------|---------------------------------------------------------------------------------|------------------------------------------------|----------------------------------|
| 21    | 1,5 µg/kg 24 weeks PEG-IFN
alpha-2b plus 800-1400 mg
ribavirin (24 weeks) | HCV-genotype 2 (n=0)
HCV genotype 3 (n=35)  | n.a.
24/35* (68.6%)           |
| 7     | 1,5 µg/kg 24 weeks PEG-IFN
alpha-2b plus 800-1400 mg
ribavirin (24 weeks) | HCV-genotype 2 (n=20)
HCV genotype 3 (n=96) | 15/20** (75%)
54/96** (56.3%) |
| 8, 21 | 1,5 µg/kg 24 weeks PEG-IFN
alpha-2b plus 800-1400 mg
ribavirin (24 weeks) | HCV-genotype 2/3
(n=151)                    | 93/151 (61,6%)                   |

\* Patients who were HCV-RNA positive (>29 IU/mL) at week 4 but HCV-RNA negative at week 12

\*\* Patients who were HCV-RNA positive (>50 IU/mL) at week 4 but HCV-RNA negative at week 12

| Ref. | Treatment regimen                                                         | Patient groups                                        | SVR without RVR                  |
|------|---------------------------------------------------------------------------|-------------------------------------------------------|----------------------------------|
| 21   | 1,5 µg/kg 24 weeks PEG-IFN alpha-2b plus 800-1400 mg ribavirin (24 weeks) | HCV-genotype 2
(n=42)
HCV genotype 3
(n=182) | n.a.
24/35* (68.6%)           |
| 6    | 1,5 µg/kg 24 weeks PEG-IFN alpha-2b plus 800-1400 mg ribavirin (24 weeks) | HCV-genotype 2
(n=51)
HCV genotype 3
(n=211) | 15/20** (75%)
54/96** (56.3%) |

\* Patients who were HCV-RNA positive (>29 IU/mL) at week 4 but HCV-RNA negative at week 12

\*\* Patients who were HCV-RNA positive (>50 IU/mL) at week 4 but HCV-RNA negative at week 12

## 9 DATA QUALITY ASSURANCE

Each involved investigator is member (regular or associate) of Hep-Net and experienced in Interferon-based therapy of patients with chronic viral hepatitis. As members of Hep-Net, the investigators take part in advanced trainings organized by the sponsor Hep-Net, regularly.

The data collected will be entered into an electronic CRF. A comprehensive validation check program will verify the data and discrepancy reports (Data Queries) will be generated accordingly for resolution by the investigator. Accurate and reliable data collection will be assured by verification and cross-check of the electronic CRFs against the investigator's records by the study monitor (source document verification), and the maintenance of a drug-dispensing log by the investigator.

## 10 ETHICAL ASPECTS

### 10.1 Local Regulations/Declaration of Helsinki

The sponsor will ensure that this study fully adheres to the principles outlined in the "Guideline for Good Clinical Practice" which has its basis in the principles of the "Declaration of Helsinki" and with the laws and regulations of the country in which the research is conducted, whichever affords the greater protection of the individual.

### 10.2 Patient Information and Informed Consent

It is the responsibility of the investigator or an authorised physician to obtain written informed consent from each individual participating in this study after adequate explanation of the aims, methods, objectives and potential hazards of the study. It must also be explained to the patients that they are completely free to refuse to enter the study or to withdraw from it at any time for any reason without any consequences for further treatment. Appropriate forms for obtaining written informed consent will be provided to the investigator by Hep-Net/designee.

If new safety information results in significant changes in the risk/benefit assessment, the consent form should be reviewed and updated if necessary. All patients (including those already being treated) should be informed of the new information, given a copy of the revised form and asked to give their consent to continue in the study.

### **10.3 Insurance**

Every patient participating in the study will be insured by ALLIANZ AG according to German Arzneimittelgesetz (AMG) § 40 Abs. 3. All subjects will be informed about their rights and obligations in regard to insurance policies before participating in the study. A copy of the insurance policies will be available for each subject.

### **10.4 Independent Ethics Committees (IEC)**

This protocol and any accompanying material provided to the patient (such as patient information sheets or informed consent) as well as any advertising will be submitted by the sponsor to an Independent Ethics Committee (IEC). Approval from the committee must be obtained before starting the study.

Any substantial modifications made to the protocol after receipt of the IEC approval must also be submitted to the Committee in accordance with local procedures and regulatory requirements.

### **10.5 Financing**

The study will be financed by the Bundesministerium für Bildung und Forschung (BMBF)-Project German Competence Network for Viral Hepatitis (Hep-Net). Study medication will be provided by MSD Sharp & Dohme GmbH.

No compensation will be given to the patients for participating in this study. Only travel expenses will be reimbursed for enrolled patients.

## **11 CONDITIONS FOR MODIFYING THE PROTOCOL**

No changes to the study protocol will be allowed unless discussed in detail with the Hep-Net Study coordinators and filed as an amendment/modification to this protocol.

Any amendment/modification to the protocol will be adhered to by the participating centre(s) and will apply to all subjects. Written IEC approval of protocol amendments is required for substantial amendments prior to implementation; modifications are submitted to IECs for information only.

## **12 SUBJECT COMPLETION**

After finishing the study, patients will be treated according to standard therapeutic procedures applicable at that time.

### **12.1 Procedures for handling patients lost to follow-up and drop-outs**

Investigators should make an attempt to contact those patients who do not return for scheduled visits or follow-up. Information gathered should be described on the Study Conclusion page of the Case Report Form and on Medication/Adverse event forms.

### **12.2 Reasons for drop-out**

It should be specified on the Study Conclusion page of the case report form which of the following possible reasons were responsible for drop-out of the patient from the study:

- Serious adverse event
- Non-serious adverse event
- Protocol violation (specify)
- Consent withdrawal, not due to an adverse event
- Migration from the study area
- Lost to follow-up
- Other (specify)

## **13 STUDY DOCUMENTATION, electronic CRF AND RECORD KEEPING**

### **13.1 Investigator's Files/Retention of Documents and Source Documents**

The Investigator must maintain adequate and accurate records to enable the conduct of the study to be fully documented and the study data to be subsequently verified. These documents should be classified into two different separate categories (1) Trial Investigator's File (TIF), and (2) patient clinical source documents.

The TIF will contain the protocol/amendments, Independent Ethics Committee and governmental approval with correspondence, sample patient information and informed consent form, general insurance conditions, signed informed consent forms from enrolled patients, drug records, patient screening and enrolment logs, signed staff curriculum vitae and authorization forms and other appropriate documents/correspondence etc.

Patient clinical source documents (usually defined by the project in advance to record key efficacy/safety parameters) would include patient hospital/clinic records, physician's and nurse's notes, original laboratory reports, ECG, and special assessment reports, consultant letters.

The investigator must keep these two categories of documents on file for at least 15 years after completion or discontinuation of the study. After that period of time the documents may be destroyed, subject to local regulations.

Should the Investigator wish to assign the study records to another party or move them to another location, Hep-Net must be notified in advance.

If the Investigator can not guarantee this archiving requirement at the investigational site for any or all of the documents, special arrangements must be made between the Investigator and Hep-Net to store these in a sealed container(s) outside of the site so that they can be returned sealed to the Investigator in case of a regulatory inspection. Where source documents are required for the continued care of the patient, appropriate copies should be made for storing outside of the site.

The investigator shall supply the sponsor/designee on request with any required background data from the study documentation or clinic records. This is particularly important for quality assurance (monitoring of source documents, audits), when errors in data transcription are suspected and in case of requests for inspections.

### **13.2 Audits and Inspections**

The Investigator should understand that source documents for this study should be made available to appropriately qualified personnel from the Hep-Net Quality Assurance Unit or its designees or to health authority inspectors after appropriate notification.

### **13.3 Case Report Forms (CRFs)**

For each patient enrolled, an electronic CRF must be completed promptly after the patients visit and signed by the (principal) investigator. This also applies to records for those patients who fail to complete the study. If a patient withdraws from the study, the reason must be noted on the CRF. If a patient is withdrawn from the study because of a treatment-limiting adverse event, thorough efforts should be made to clearly document the outcome.

All forms should be typed or filled out using indelible ink, and must be legible. Errors should be crossed out but not obliterated, the correction inserted, and the change initialled and dated by the investigator or his/her authorized delegate. The investigator should ensure the accuracy, completeness, legibility, and timeliness of the data reported to the sponsor in the CRFs and all required reports.

## **14 MONITORING THE STUDY**

Monitoring of the study is required according to ICH-GCP and AMG and is important to guarantee a valid study.

### **14.1 Direct Source Data Verification**

On-Site-monitoring: 10 % of all filled-in case report forms in each study site will undergo a 100 %-verification to the source of data. Further case report forms will only be checked with respect to key data, e.g. informed consent and inclusion/exclusion criteria. Further details will be described in a trial specific monitoring plan.

## **15 CONFIDENTIALITY OF TRIAL DOCUMENTS AND PATIENTS RECORDS**

The investigator must assure that patients' anonymity will be maintained and that their identities are protected from unauthorized parties. The investigator should keep a patient enrolment log relating codes to the names of patients. The investigator should maintain documents not for submission to Hep-Net, e.g., patients written consent forms, in strict confidence.

## **16 PUBLICATION OF DATA**

The results of the study shall be published in an international peer-reviewed journal. The publication rules of the standing orders of the German Competence Network for Viral Hepatitis (Hep-Net) shall be applied.

The trial will be registered at a study register (i.e. [www.clinicaltrials.gov](http://www.clinicaltrials.gov)) according to current publication guidelines.

